### **5.3 Escape medication**

- Clonidine (maximum dosage of 3 dd 0.15 mg)

## 6 INVESTIGATIONAL MEDICINAL PRODUCT

### 6.1 Name and description of investigational medicinal product

Ramipril (tritace) is an inhibitor of the angiotensin converting enzyme (ACE) which converts angiotensin I to angiotensin II. The levels of angiotensin I and II decrease and the plasma renin activity increases.

Following oral administration ramipril is rapidly absorbed from the gastrointestinal tract; peak plasma concentrations of ramipril are reached within one hour. Peak plasma concentrations of the active metabolite, ramiprilat, are reached within 2 - 4 hours. Plasma concentrations of ramiprilat decline in a polyphasic manner. The effective half-life of ramiprilat after multiple once daily administration of ramipril is 13 - 17 hours for 5 -10 mg ramipril and markedly longer for lower doses, 1.25 - 2.5 mg ramipril. This difference is related to the long terminal phase of the ramiprilat concentration time curve observed at very low plasma concentrations. This terminal phase is independent of the dose, indicating a saturable capacity of the enzyme to bind ramiprilat. Steady-state plasma concentrations of ramiprilat after once daily dosing with the usual doses of ramipril are reached by about the fourth day of treatment. Ramipril is almost completely metabolized and the metabolites are excreted mainly via the kidneys. In addition to the bioactive metabolite, ramiprilat, other, inactive metabolites have been identified, including diketopiperazine ester, diketopiperazine acid and conjugates.

Aliskiren (rasilez) is a selective inhibitor of the enzyme renin and thereby targeting the conversion of angiotensinogen to angiotensin I, resulting in decreased levels of angiotensin I, II and renin. Aliskiren thereby lowers systolic and diastolic blood pressure.

The single and multiple-dose oral pharmacokinetics of aliskiren has been investigated over the dose range 40 to 1800 mg (aliskiren hemifumarate) in healthy subjects and in patients. Maximum plasma concentrations of aliskiren were observed between 2 and 4 h post-dose (median tmax). Half life ranged from 34 to 41 hours. Mean absolute bioavailability was 2.6% (for a 75 mg hard gelatin tablet formulation). Administration of aliskiren together with food decreased mean Cmax and AUC0-inf by 81 and 62%, respectively. After multiple dosing, the mean terminal half-life was between 23 and 36 h. Excretion of unchanged aliskiren in urine was 0.11 to 0.45%. No significant interaction has been found with co-administration of irbesartan, furosemide, digoxin, ramipril and hydrochlorothiazide. Co-administration of metformin or amlodipine resulted in less than 30% change in Cmax or AUC of aliskiren. When aliskiren was co-administered with furosemide, the AUC and Cmax of furosemide were reduced by 28% and 49%

respectively. Co-administration of ketoconazole with aliskiren resulted in increased plasma levels of aliskiren (AUC and Cmax by 76% and 81% respectively). Co-administration of atorvastatin with aliskiren had no effect on the steady-state pharmacokinetics of atorvastatin or its two active metabolites, but there was an increase in steady-state Cmax and AUC by approximately 50%. Studies were also performed with cimetidine, atenolol, acenocoumarol and celecoxib. There were no clinically relevant changes in the pharmacokinetic parameters of any of these drugs, or aliskiren, when combined or when given alone. Aliskiren should not be given together with strong Pgp inhibitors like cyclosporin.

## **6.2 Summary of findings from non-clinical studies**

This is not applicable as ramipril and aliskiren are both registered for treatment of blood pressure and progression of renal disease in humans.

## **6.3 Summary of findings from clinical studies**

Aliskiren inhibits the RAAS in a dose dependent manner. The evidence for RAAS blockade is based on the effects of aliskiren on plasma renin activity, angiotensin I and II levels, urinary aldosterone levels and plasma rennin concentration. Plasma PRA is a direct measure of the formation of Ang I in the plasma. Plasma renin concentration (PRC), measures the concentration of immunoactive renin in the plasma. Phase 2 and 3 clinical studies involving over 9000 subjects with hypertension have demonstrated that aliskiren provides effective long-term BP lowering with a good safety and tolerability profile at doses of 150 and 300 mg/day. Aliskiren inhibits PRA by up to 80% following both single and multiple oral dose administration. Similar reductions in PRA are observed when aliskiren is administered in combination with agents that increase PRA, including diuretics, ACEi and ARB's, despite greater increases in PRC. Moreover, PRA inhibition and BP reductions persist for 2 to 4 weeks after stopping aliskiren treatment.

After 8 weeks of treatment of diabetic patients with hypertension [CSPP100A2307], PRA was significantly increased from baseline with ramipril monotherapy (10 mg, 106%;  $p < 0.001$  vs baseline). In contrast, aliskiren monotherapy produced a statistically significant reduction from baseline in PRA of 66% (300 mg,  $p < 0.001$ ). Aliskiren-based therapy also reduced PRA despite causing a rise in plasma renin concentration [CSPP100A2306]. At the end of the 26-week treatment of mild to moderate hypertension patients, aliskiren-based therapy (aliskiren 150 or 300 mg) reduced PRA by 63% (relative to baseline), whereas ramipril-based therapy (ramipril 5 or 10 mg) increased PRA by 143%.

## **6.4 Summary of known and potential risks**

### Ramipril

Ramipril is approved for the treatment of hypertension by EMEA, FDA and Dutch registration board (CVZ). Generally, adverse reactions with ramipril (tritace) have been mild and transient, and did not require discontinuation of therapy. The most frequently reported adverse reactions are nausea, dizziness and headache. Uncommonly drowsiness, light headedness or impaired reactions may occur. Reactions such as peripheral edema, tinnitus, fatigue, visual disturbances, sweating, disturbed hearing, and disturbed orthostatic regulation are rare. Symptomatic hypotension accompanied by dizziness, weakness and nausea may occur after the initial dose of Ramipril and after an increase in the dose of ramipril. It has been rarely observed, but may occur in severely salt/volume-depleted patients. Ramipril can result in hyperkalemia. Data on pharmacokinetics are given in paragraph 6.1.

### Aliskiren

Aliskiren (rasilez) has been approved by EMEA, FDA and Dutch registration board (CVZ) for and has been prescribed in clinical setting to treat hypertension and progression of renal disease. No serious side effects are expected at the dosage used in this study. Possible side effects of aliskiren are orthostatic hypotension, diarrhoea and rash. Aliskiren can result in hyperkalemia. Data on pharmacokinetics are given in paragraph 6.1.

## **6.5 Description and justification of route of administration and dosage**

Aliskiren and ramipril are fully absorbed from the digestive tract and can therefore be orally administered.

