
Patients will be instructed to take the study medication once daily, in the morning, except on study days; on those days, the study drug will not taken before renal hemodynamic measurements at the hospital (between 8:00 and 9:30 a.m.). In total, patients visit the outpatient nephrology clinic on a more regular basis than standard patient care (5 hospital visits in a total study duration of 26 weeks).

In summary, this is the study protocol (with treatment sequence randomized):

[figure not shown]

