### 5.2 Use of co-intervention (criteria adapted from ARIA-study: METc 2010.114)

Use of the following treatments is NOT allowed after the start of the study as these medications may interfere with the evaluation of safety, tolerability and/or efficacy. Patients who are receiving such medication(s) should be excluded, or if ethically justified, the medication(s) may be withdrawn according to the manufacturer's/investigator's instructions prior to start of the screening period. Withdrawal of medication is done after consultation with the patient and patients' physician

- RAAS-medication, diuretics or  $\beta$ -blockers
  - NSAIDS/COX-2 inhibitors. Continuous use is not allowed during the trial. Acute and intermittent use of acetaminophen and aspirin is permitted throughout the trial
  - Oral corticosteroids. Inhaled, topical and nasal corticosteroid preparations may be used as needed
  - Antipsychotic agents (e.g., clozapine, haloperidol or phenothiazines)
  - Thyroid medication and/or low dose hormone replacement therapy, and statins unless these have been stable maintenance doses for 3 months prior to study
  - Chronic administration (defined as administration >3 days per week) of sympathomimetic drugs such as those found in nasal decongestants (e.g., pseudoephedrine, phenylpropanolamine) and bronchodilators (e.g., metaproterenol). Occasional use of these drugs (if not within 48 hours of a scheduled visit) is allowed

- Ergot and serotonin (5-hydroxytryptamine) receptor agonists (e.g., sumatriptan).
- Phosphodiesterase type 5 (PDE5) inhibitors such as sildenafil (Viagra), vardenafil (Levitra), and tadalafil (Cialis) are not allowed within 48 hours prior to any scheduled visit
- Antiarrhythmic drugs including digoxin
- Cholestyramine and colestipol resins
- Potent and moderate P-gP inhibitors for example cyclosporine. For moderate P-gP inhibitors such as ketoconazole and verapamil, caution should be exercised

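### Section 6.5 states complete absorption, against the aliskiren figures in section 6.1; no intake rule addresses the 62% food effect, and the P-gP inhibitor rule in section 5.2 contradicts itself

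*Protocol*

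**What the plan says.** **Justification of route and dosage (Protocol 6.5).** The section is a single sentence: "Aliskiren and ramipril are fully absorbed from the digestive tract and can therefore be orally administered".

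**Pharmacokinetics (Protocol 6.1).** For aliskiren: "Mean absolute bioavailability was 2.6% (for a 75 mg hard gelatin tablet formulation"). On food: "Administration of aliskiren together with food decreased mean C max and AUC 0-inf by 81 and 62%, respectively". On ketoconazole: "Co-administration of ketoconazole with aliskiren resulted in increased plasma levels of aliskiren", with AUC up 76% and Cmax up 81%. For ramipril the section describes rapid absorption, metabolism and half-life, but gives no bioavailability figure and no food or P-gP result.

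**Intake (Protocol 3, 5.1, 6.6).** Section 3: "Patients will be instructed to take the study medication once daily, in the morning, except on study days". On study days the dose is held back until the renal measurements. Sections 5.1 and 6.6 give dose and once-daily frequency. None of the three relates intake to food.

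**Co-medication (Protocol 5.2, 4.3).** Section 5.2 opens a list of prohibited treatments. One bullet in it names potent and moderate P-gP inhibitors and continues: "For moderate P-gP inhibitors such as ketoconazole and verapamil, caution should be exercised". Section 4.3 excludes, in general terms and at entry, medication that might significantly alter absorption, distribution, metabolism or excretion.

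**The concern.** The only justification offered for route and dosage disagrees with the protocol's own data on one of the two drugs. The disagreement has a practical side. If absorption were complete, the circumstances of intake would hardly matter and a bare morning-dose instruction would do. Section 6.1 shows that they matter a good deal for aliskiren.

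The cross-over does not remove this. A patient who always doses with breakfast does so in both periods, but the protocol reports an effect of food only for aliskiren, so the aliskiren-minus-ramipril difference may depend on that habit. The possible result is a diluted or more variable aliskiren effect in a trial planned on 14 completers, with no replacement once treatment has started (section 7.5). The study parameters in section 7.1 include no aliskiren concentration. Plasma renin activity would give at most an indirect sign of low exposure, so a small difference would be hard to interpret.

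Separately, staff reading the P-gP bullet cannot tell whether ketoconazole or verapamil is forbidden or tolerated.

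**Working it through.** **1. Exposure ratios, from section 6.1**

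- AUC with food relative to without: 1 − 0.62 = 0.38. Cmax: 1 − 0.81 = 0.19.
- Spread in AUC between compliant patients from food alone: 1/0.38 = 2.6-fold.
- AUC with ketoconazole relative to without: 1.76.

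**2. The P-gP rule, side by side**

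- Head of the list in 5.2 plus the first half of the bullet: moderate inhibitors are prohibited.
- Second half of the bullet: caution with two named moderate inhibitors, which implies that they may be used.
- Section 4.3: a general exclusion at entry, which names no P-gP inhibitor and does not settle use that begins during the study.

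The first two cannot both hold, and the third does not decide between them.

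**3. The plan's sample size, as reference for an illustration**

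Inputs from section 4.4: ERPF rises by 13 ± 11 ml/min with ACE inhibition and 47 ± 17 ml/min with aliskiren; baseline SD 35; 14 completers; 90% power; α = 0.05 (two-sided per the descriptive statistics section). The difference is 47 − 13 = 34 ml/min.

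With a paired t-test (noncentral t) and 35 taken as the SD of the within-patient difference, 90% power needs n = 14, and power at 14 is 0.92. This reproduces the plan's figure, and 14/0.9 = 15.6 rounds up to the 16 included. However, 35 is given as the SD of baseline ERPF. The stated change SDs at zero correlation give √(11² + 17²) = √410 = 20.2, for which 6 patients suffice. Both SDs are carried below.

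**4. Hypothetical effect on power**

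Assumptions, none of them in the protocol: ERPF response to aliskiren is proportional to AUC; the +47 ml/min was obtained fasted; the ramipril effect does not change with food; a share f of patients takes every dose with food.

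- Mean difference = 47 × [(1 − f) + 0.38f] − 13.
- Mixed intake adds variance f(1 − f) × (47 × 0.62)² = f(1 − f) × 29.1², which is about 159 at f = 0.25 and 212 at f = 0.5.

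| Share fed | Difference (ml/min) | Power, SD 35 | SD 35 plus mixture variance | Power, SD 20.2 | SD 20.2 plus mixture variance |
|---|---|---|---|---|---|
| 0 | 34.0 | 0.92 | 0.92 | >0.99 | >0.99 |
| 25% | 26.7 | 0.75 | 0.70 | >0.99 | 0.97 |
| 50% | 19.4 | 0.49 | 0.43 | 0.91 | 0.77 |
| 100% | 4.9 | 0.08 | 0.08 | 0.13 | 0.13 |

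If ERPF response is flat over this range of exposure, the first row applies throughout.

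**The case against.** Six points can be made on the other side.

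- *Bioavailability is not the fraction absorbed, and 2.6% belongs to a 75 mg formulation, not to the 300 mg dose of this trial.* Both are true. The 2.6% alone does not prove incomplete absorption. The food effect is the stronger evidence, and nothing in the protocol supports complete absorption of aliskiren.
- *Ketoconazole is controlled.* A reader might infer from the caution sentence that the protocol leaves it free. It does not: its class is on the prohibited list, and the entry exclusion in 4.3 covers such drugs in general terms. The defect is contradiction, not absence.
- *The exposure range is wider than 2.6-fold.* Combining fed intake with ketoconazole gives 1.76/0.38 = 4.6-fold, but calling every such patient compliant requires the permissive reading of a contradictory bullet. The 2.6-fold food range does not depend on that reading. Section 6.1 also says of atorvastatin that "there was an increase in steady-state C max and AUC by approximately 50" percent, and stable statins are allowed, but that sentence does not say outright whose exposure rises, so nothing is built on it here.
- *The problem touches aliskiren alone.* That is an inference too. The protocol is silent on food and P-gP effects for ramipril, and silence does not show that there is none. What follows is only that cancellation cannot be assumed.
- *The trial is underpowered because of food.* The documents do not support this. They give no relation between ERPF and exposure and do not say how the +47 ml/min was obtained. The apparent loss also depends heavily on the SD: at 50% fed, power is 0.43 to 0.49 with one and 0.77 to 0.91 with the other.
- *Food conditions may be set on the label or in patient instructions.* Possibly; those are not at hand. The protocol's own intake instruction should still agree with its pharmacokinetic section.

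**Conclusion.** The point stands as a conflict of text with text. Section 6.5 does not agree with section 6.1, the intake instructions do not address a food effect that the protocol itself reports, and the P-gP bullet in section 5.2 both prohibits and tolerates moderate inhibitors. On the protocol's figures, food alone lets aliskiren AUC vary about 2.6-fold among patients who all follow the instructions.

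The consequence for the ERPF comparison has a plausible direction (a diluted or noisier aliskiren effect) but no size that the documents can supply. The power figures are illustrative and run from no loss to nearly complete loss, depending on assumptions that the protocol neither states nor excludes. The passages should be reconciled because doing so is cheap and removes an avoidable source of variation, not because a loss of power has been shown.

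**What to change.** 1. Correct section 6.5 so that it agrees with the aliskiren figures in section 6.1.
2. Reconcile the intake instruction in sections 3, 5.1 and 6.6 with the food effect, so that one stated intake condition applies to every patient in both periods. The double-dummy design allows the same instruction throughout.
3. Reconcile the P-gP bullet in section 5.2 with the heading of its own list and with the exclusion in section 4.3, so that it says one thing about moderate inhibitors.

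Which intake condition and which co-medication rule apply is for the sponsor's clinical team; none is proposed here.

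Cost: protocol and patient-instruction wording, and a slightly more restrictive intake routine for patients. No added visits, tests or patients.

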## **6.6 Dosages, dosage modifications and method of administration**

Aliskiren (tablets): 300 mg once daily, orally.

Ramipril (tablets): 10 mg once daily, orally.

## **6.7 Preparation and labelling of Investigational Medicinal Product**

Study medication (aliskiren, ramipril and matching placebo's) will be provided by Novartis and repacked and labelled by the pharmacy unit of the University Medical Center Groningen (UMCG).

**6.8 Drug accountability**

All study medication will be stored at room temperature at the pharmacy department of the University Medical Center Groningen (UMCG). Study medication will be collected from the pharmacy department by the coordinating investigator once a week. Non-used medication will be returned to the pharmacy department where it will be destructed.

## 7 METHODS

### 7.1 Study parameters/endpoints

#### 7.1.1 Primary study parameters

- Renal hemodynamics (GFR, ERPF, FF)
- Blood pressure

#### 7.1.2 Secondary study parameters

- Volume status (ECV)
- RAAS parameters (plasma renin activity, plasma renin concentration, angiotensin II, aldosteron)
- Urinary and serum kidney injury markers, such as, but not limited to, TGF $\beta$ , KIM-1, NGAL and NAG.

#### 7.1.3 Other study parameters

- routine blood biochemistry (renal function, electrolytes, liver enzymes, lipid profile, glucose, volume parameters) and full blood cell count
- routine urinary chemistry (creatinine, albumin, urea, potassium and sodium)

### 7.2 Randomisation, blinding and treatment allocation

Treatment sequence of aliskiren and ramipril will be randomized by computer randomization with a batch size of 2. Patients are treated double-dummy.

### 7.3 Study procedures

#### Physical examination

Patients will be subjected to physical examination by the investigator at study inclusion. This physical examination entails a routine investigation of heart, lungs and abdomen.

#### Renal hemodynamic measurements

At start and end of each treatment period, glomerular filtration rate (GFR) and effective renal plasma flow (ERPF) are measured by constant infusion of radio labeled tracers,  $^{125}\text{I}$ -iothalamate, and  $^{131}\text{I}$ hippurate, respectively, the patients being in a quiet room, in the semi-supine position. After drawing a blank blood sample, a priming solution containing 0.04 mL/kg body weight of the infusion solution (0.04 MBq of  $^{125}\text{I}$ iothalamate and 0.03MBq of  $^{131}\text{I}$ -hippurate) plus an extra of 0.06 MBq of  $^{125}\text{I}$ -iothalamate is given at 0800

hours, followed by infusion at 12 mL/h. In order to attain stable plasma concentrations of both tracers, a 2-hour stabilization period followed, after which baseline measurements start at 1000 hours. The clearances are calculated as  $(U \times V)/P$  and  $(I \times V)/P$ , respectively.  $U \times V$  represents the urinary excretion of the tracer,  $I \times V$  represents the infusion rate of the tracer, and  $P$  represents the tracer value in plasma at the end of each clearance period. This method corrects for incomplete bladder emptying and dead space, by multiplying the urinary clearance of  $^{125}\text{I}$ -iothalamate with the ratio of the plasma and urinary clearance of  $^{131}\text{I}$ -hippurate. The filtration fraction (FF) is calculated as the ratio of GFR and ERPF and expressed as percentage. This measurement is the Gold Standard for renal hemodynamics and routinely performed in the University Medical Center of Groningen (UMCG).

#### Blood pressure measurements

At start and end of each treatment period, blood pressure is measured over a period of 24hr by an ambulant device (Spacelab). Furthermore, blood pressure is measured at 1-minute intervals for 15 minutes with a semi-automatic device (Dinamap; DE Medical systems, Milwaukee, WI) at study inclusion and during renal hemodynamic measurements. In addition, blood pressure is measured 2 weeks after start of each treatment period and 3 weeks after start of each wash-out period.

#### 24hr urine collection

Patients are asked to collect 24hr urine at study and at start and end of each treatment period to monitor microalbuminuria and measure biomarkers. In total, 24hr urine is collected 5 times in course of this study.

#### Venapuncture

Blood samples are obtained by venapuncture at study inclusion (20 cc) and at start and end of each treatment period (each 50 cc). Furthermore, 2 weeks after start of each treatment period, a venapuncture is performed to check serum potassium (4 cc). At the end of this study, approximately 230 cc of blood is collected from each patient.

#### Laboratory measurements

All routine laboratory measurements of this study will be assessed at the laboratory of the University Medical Center Groningen (UMCG).

### **7.4 Withdrawal of individual subjects**

Study drug must be discontinued for a given patient if the investigator determines that continuing would result in a significant safety risk for that patient or if he/she thinks that continuation would be detrimental to the patient's well-being.

#### 7.4.1 Specific criteria for action and withdrawal

Uncontrolled hypertension According to criteria written in study design (paragraph 3) systolic and diastolic blood pressure must remain lower than 180 and 110 mmHg, respectively. When blood pressure exceeds the before mentioned values during run-in, the patient will be considered a screen failure and prior antihypertensive medication is restarted. If the blood pressure exceeds these values during the study despite rescue medication, the patient will be withdrawn from the study (criteria adapted from ARIA-study: METc 2010.114).

Hypotension Two weeks after start of treatment period, blood pressure is measured for 15 minutes using a semi-automatic device (Dinamap). Hypotension is defined as systolic blood pressure <100 mmHg or a diastolic blood pressure <60 mmHg. Patients with hypotension and orthostatic complaints will be closely monitored and evaluated during the course of the study. If clinically warranted, these patients should be permanently discontinued from the study (criteria adapted from ARIA-study: METc 2010.114).

Hyperkalemia Two weeks after start of treatment period, a venapuncture is performed to check for serum potassium level. A potassium levels above 5.5 mmol/L needs to be reassessed with a second venapuncture within 5 days. After reassessment, patients with a serum potassium level between 5.0 and 6.0 mmol/L will start with dietary potassium restriction and serum potassium is checked every 2-weeks. A serum potassium  $\geq 6.0$  mmol/L will in all cases result in immediate discontinuation of study medication (criteria adapted from ARIA-study: METc 2010.114).

All patients who discontinue study drug, including those who refuse to return for a final visit, will be contacted for safety evaluations during the 30 days following the last dose of study drug. Patients who discontinue study drug should be considered withdrawn from the study after the final visit assessments are performed or when it is clear that the patient will not return for these assessments. Patients who discontinue during the treatment period should be scheduled for a visit as soon as possible, at which time all of the assessments listed for the final visit will be performed.

